## Abstract

**Background**
 Venous thromboembolism (VTE) in hospitalized medically ill patients is a significant cause of morbidity and mortality. Guidelines suggest that VTE and bleeding risk assessment models (RAMs) should be integrated into the clinical decision-making process on thromboprophylaxis. However, poor evidence is available comparing the use of a RAM versus clinical judgement in evaluating VTE and bleeding occurrence.

**Methods**
 Reducing Important Clinical Outcomes in hospitalized medical ill patients (RICO) is a multicenter, cluster-randomized, controlled clinical trial (ClinicalTrials.gov Identifier: NCT04267718). Acutely ill patients hospitalized in Internal Medicine wards are randomized to the use of RAMs—namely the Padua Prediction Score and the International Medical Prevention Registry on Venous Thromboembolism Bleeding Score—or to clinical judgement. The primary study outcome is a composite of symptomatic objectively confirmed VTE and major bleeding at 90-day follow-up. Secondary endpoints include the evaluation of clinical outcomes at hospital discharge and the assessment of VTE prophylaxis prescription during the study period. In order to demonstrate a 50% reduction in the primary outcome in the experimental group and assuming an incidence of the primary outcome of 3.5% in the control group at 90-day; 2,844 patients across 32 centers will be included in the study.

**Discussion**
 The RICO trial is a randomized study of clinical management assessing the role of RAMs in hospitalized medical ill patients with the aim of reducing VTE and bleeding occurrence. The study has the potential to improve clinical practice since VTE still represents an important cause of morbidity and mortality in this setting.

## Introduction

Venous thromboembolism (VTE) in hospitalized patients with a medical illness is a significant cause of morbidity and mortality.
1
Recent European estimates report an annual incidence of VTE ranging from 104 to 183 per 100,000 person-years.
2
VTE is also associated with reduced survival.
2
The rationale for thromboprophylaxis in hospitalized, medically ill patients is supported by a wealth of evidence showing decreased pulmonary embolism and symptomatic deep vein thrombosis rates without significant increases in major bleedings.
3
4
In spite of this, thromboprophylaxis is generally underprescribed
1
as only 40 to 75% of eligible patients receive VTE prophylaxis.
5
6
7
Reasons accounting for suboptimal prescription of thromboprophylaxis may derive from an underestimation of the risk of VTE or from a risk–benefit evaluation, in terms of thrombotic and bleeding risk, that is sometimes challenging in patients hospitalized in Internal Medicine (IM) wards.

Most recent guidelines suggest that VTE and bleeding risk assessment models (RAMs) should be integrated into the clinical decision-making process.
4
To date, a number of RAMs evaluating VTE risk in hospitalized patients is available, as summarized in
Table 1
.
8
9
10
11
12
13
14
15
16
17
18
19
20
The Padua Prediction Score and the International Medical Prevention Registry on Venous Thromboembolism (IMPROVE) VTE score are considered the best available RAMs to evaluate the risk for VTE in hospitalized, medically ill patients
15
18
(
Table 1
). Padua Prediction Score includes a number of differently weighed conditions known to increase VTE risk, with a final score ≥4 suggesting a high risk for VTE.
8
The IMPROVE Bleeding Score was developed and validated to assess the risk of bleeding in a population of hospitalized, medically ill patients.
11
Among these patients, an IMPROVE Bleeding Score ≥ 7 conferred an increased risk of bleeding.
11
In a large single-center study (1,761 patients) focused on in-hospital medical patients, more than three-fourths of the included patients were at high VTE risk and almost 90% of them were at low bleeding risk.
10

**Table 1 TB22060028-1:** Main risk assessment models for venous thromboembolism prediction in hospitalized, medically ill patients

RAM	Authors	Type of study	Reference
*VTE RAM*			
Geneva Risk Score	Chopard et al	Retrospective cohort study (for derivation)	10
	Nendaz et al	Prospective cohort study (for validation)	14
Simplified Geneva Risk Score	Blondon et al	Prospective cohort study (for validation)	9
Padua Prediction Score	Barbar et al.	Prospective cohort study	8
	Vardi et al	Prospective cohort study (for validation)	18
IMPROVE VTE	Spyropoulos et al	Prospective cohort study	17
	Rosenberg et al	Case–control study (for validation)	15
	Mahan et al	Retrospective cohort study (for validation)	34
	Greene et al	Retrospective, cohort study (for validation)	35
Kucher RAM	Kucher et al	Randomized controlled study	13
	Woller et al	Retrospective cohort study (for validation)	19
MITH RAM	Zakai et al	Retrospective cohort study	20
*Bleeding RAM*			
IMPROVE Bleeding	Decousus et al	Prospective cohort study	11
	Hostler et al	Prospective cohort study (for validation)	12
	Rosenberg et al	Prospective cohort study (for validation)	16

Abbreviations: IMPROVE, International Medical Prevention Registry on Venous Thromboembolism; MITH, Medical Inpatients and Thrombosis; RAM, risk assessment model; VTE, venous thromboembolism.

More recently, in the real-world Federazione delle Associazioni dei Dirigenti Ospedalieri Internisti (FADOI)-NoTEVole (Studio nazionale, osservazionale retrospettivo, sul pattern prescrittivo della profilassi del tromboembolismo venoso in Medicina Interna alla dimissione) study, almost half of the patients admitted to IM division carried a high thrombotic score according to Padua Prediction Score, but only 7.2% presented a high bleeding risk according to IMPROVE Bleeding Score.
21
These results suggest that VTE prophylaxis can be prescribed to a large number of hospitalized, medical patients with very limited harm.

Poor evidence is available comparing the use of a RAM versus clinical judgement in choosing whether or not to prescribe VTE prophylaxis. In a single-center, prospective, quasi-randomized study, the adoption of Padua Prediction Score was associated with a 50% reduction in the incidence of VTE (either symptomatic or asymptomatic) compared with clinical judgement, with no differences in terms of bleeding and death from all cause.
12
These preliminary results need a confirmation in a large, multicenter study in order to test the appropriateness of VTE prophylaxis through a systematic application of RAMs, and to compare it with clinical judgement.

## Study Rationale and Methods

### Trial Design and Objectives

FADOI promoted the Reducing Important Clinical Outcomes in hospitalized medical ill patients (RICO) study, a multicenter, cluster-randomized, controlled clinical trial (ClinicalTrials.gov Identifier: NCT04267718) involving a large number of IM divisions affiliated to FADOI across the whole Italian territory. The aim was to evaluate the systematic use of RAMs, that is, Padua Prediction Score (PPS) and IMPROVE Bleeding Score (IBS), compared with clinical judgement as a guide for prescribing VTE prophylaxis, and the relevant clinical outcomes (thromboembolic and hemorrhagic events).

### Study Endpoints

The primary endpoint of the study is to assess the efficacy of a systematic evaluation of the thromboembolic and bleeding risk in reducing the composite rate of thromboembolic and hemorrhagic events in hospitalized, acutely ill medical patients at a 90-day follow-up.

Secondary endpoints include (i) the evaluation of clinical outcomes (VTE, major bleeding, cardiovascular events) at the time of hospital discharge (i.e., discharge at home, transfer to another unit, or death) and (ii) the assessment of VTE prophylaxis prescription during hospital stay and at the time of discharge.

As thromboprophylaxis has been shown to have the potential to reduce arterial events as well,
22
23
24
25
information about arterial events (e.g., stroke, acute myocardial infarction, peripheral artery disease) has been collected and will be analyzed as an exploratory outcome.

### Patients

#### Inclusion Criteria

Patients are included in the present study if (i) they are 18 years or older, (ii) they are hospitalized for any reason in an IM division, and (iii) they sign the informed consent.

#### Exclusion Criteria

Patients are not included in the study if (i) the expected hospital stay is less than 48 hours, (ii) they had any indication for anticoagulant therapy, or (iii) the expected life expectancy is less than 90 days.

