#### Definition of the Experimental Group

This group includes those centers randomized to systematically evaluate VTE prophylaxis in all eligible patients using the Padua Prediction Score and IMPROVE Bleeding Score within 48 hours from hospitalization.

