### Study Procedures

Centers that do not adopt any standardized procedure for the application of PPS and/or IBS are selected for the study. These centers are then randomized in a 1:1 ratio to the experimental and control arms of the study. Eligible patients in centers randomized to the experimental group are evaluated within 48 hours from hospital admission by using Padua Prediction Score and IMPROVE Bleeding Score. Centers randomized to the control group evaluate eligible patients according to clinical judgement and current clinical practice. In order to minimize any study bias, it is strongly recommended that health care personnel not involved in the patient's clinical evaluation fills the study-specific electronic case report form. All patients, irrespective of allocation arm, are assessed at a 90-day follow-up in order to evaluate the occurrence of thrombotic, hemorrhagic, or other major clinical events (deaths, cardiovascular events), and the use of VTE prophylaxis.

Study duration was originally set to 1 year. However, due to coronavirus disease 2019 pandemic, the study frame was extended to additional 2 years in order to achieve the needed sample size.

Formal approval from the Ethics Committee (EC) of the participating Centers will be obtained before any study procedure.

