#### Informed Consent

The investigator must explain to each subject (or legally authorized representative) the nature of the study, its purpose, the procedures, the expected duration, the potential risks and benefits involved, and any discomfort it may entail. Each subject must be informed that participation in the study is voluntary and that he/she may withdraw his/her consent for the study at any time. Consent withdrawal will not affect his/her subsequent treatment or relationship with the attending physician. This informed consent is given by means of a standard written statement in nontechnical language. The subject should read and consider the statement before signing and dating, and should be given a copy of the signed document. If written consent is not possible, oral consent can be obtained if witnessed by a signed statement from one or more people not involved in the study. It should also be mentioned why the patient was unable to sign the form. No subject can enter the study before his/her informed consent has been obtained.

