#### Statistical Analysis

Data will be analyzed and reported using the Consolidated Standard of Reporting Trials and the International Conference on Harmonisation E9 guidelines. All primary analyses will be on an intention-to-treat basis including all randomized participants.

Baseline characteristics, collected at the time of enrollment, will be cross-tabulated, according to the randomized group to check for appropriate balance and provide an overview of the study population. Baseline characteristics will be summarized as mean and standard deviation for continuous variables and as frequencies and percentages for categorical ones.

The primary outcome (proportion of thromboembolic and hemorrhagic events at a 90-d follow-up after hospital discharge) will be analyzed through an univariate logistic regression analysis to check for variables differing between groups. Variables significant at
*p*
≤ 0.10 will be included as covariates in the multilevel logistic regression model that takes into account the clustered nature of the data. As RICO is a randomized trial, we do not have a priori potential confounders. A propensity score analysis as an additional sensitivity analysis will be also performed. Considering the potential risk of an unbalanced recruitment across participating centers, the use of a multilevel logistic regression model is solid in case of unequal cluster size.
27
Secondary outcomes will be compared between groups and follow the approach detailed above for primary outcome.

Numbers and percentages of adverse events (AEs) and serious AEs will be cross-tabulated with allocated group. According to the study protocol and the primary outcome of the study, thromboembolic and hemorrhagic events will not be considered AEs.

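### The analysis section rules out a priori confounders because the trial is randomised, but patients are recruited after their centre's arm is set; baseline risk factors should be fixed in the primary model, not screened at p ≤ 0.10

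*Protocol article*

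**What the plan says.** All places are in the protocol article.

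- **Allocation.** Under Study Procedures, centres without a standardised scoring procedure are selected, and "These centers are then randomized in a 1:1 ratio to the experimental and control arms of the study". Patients are assessed after that: "Eligible patients in centers randomized to the experimental group are evaluated within 48 hours from hospital admission".
- **Entry of patients.** Inclusion requires that "they sign the informed consent". Under Informed Consent, "The investigator must explain to each subject (or legally authorized representative) the nature of the study", and "No subject can enter the study before his/her informed consent has been obtained". Two of the three exclusion criteria are forecasts by staff: a short expected stay, and that "the expected life expectancy is less than 90 days".
- **Visibility of the arm.** The experimental group consists of "centers randomized to systematically evaluate VTE prophylaxis in all eligible patients using the Padua Prediction Score and IMPROVE Bleeding Score"; control centres use clinical judgement. The one stated measure against bias concerns who completes the electronic case report form.
- **Analysis.** Statistical Analysis plans a baseline table by arm, a univariate logistic screen with a p ≤ 0.10 threshold that feeds covariates into the multilevel logistic model, and a propensity score as a sensitivity analysis. Between the screen and the propensity score stands the sentence "As RICO is a randomized trial, we do not have a priori potential confounders".
- **Data.** Under Observation and Measurements, age, comorbidities, history of VTE and of recent bleeding, functional status and laboratory tests are collected for every patient. The two risk scores are recorded in the experimental arm only.

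**The concern.** Freedom from a priori confounding is a property of designs in which the unit that is analysed is allocated after, or independently of, its entry. Here the centre is allocated and the patient is recruited later, by an investigator who in all likelihood knows the arm. The masking status is not stated; I infer it from the intervention being an open ward procedure.

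Who is approached, who consents, and who is judged likely to stay 48 hours or live 90 days can all differ by arm, and each plausibly tracks the risk of VTE or major bleeding. Intention-to-treat does not help with this, because the set contains only those who were enrolled.

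The practical consequence is the covariate rule. Having ruled out known confounders, the plan lets the data choose the adjustment set for the primary result. If baseline risk differs between arms and the screen misses part of it, the primary odds ratio mixes recruitment with the effect of the scores.

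**Working it through.** **1. The plan's own figures.** Sample size inputs: 3.5% in control, a 50% reduction (1.75%), 80% power, two-sided 5%, ICC 0.001, 16 clusters of at least 90 per arm, 2,844 in total.

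- n per arm without clustering (unpooled) = (1.960 + 0.842)² × (0.035×0.965 + 0.0175×0.9825) / 0.0175² ≈ 1,306.
- Design effect at 90 per cluster = 1 + 89×0.001 = 1.089, and 1,306 × 1.089 ≈ 1,422 per arm, or 2,844.
- Power at 2,844 (mean cluster 88.9, design effect 1.088, effective n = 1,422/1.088 ≈ 1,307 per arm) is 79.9%.

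The figure is reproduced before any allowance for dropout. That is a separate matter and does not bear on this point. I use 1,422 per arm below.

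**2. Does the sentence follow from the design?** Set side by side: centres are allocated; patients then qualify and consent individually; the arm governs open ward practice; no a priori confounders are said to exist because of randomisation. The last does not follow from the first three. Randomisation protects centre characteristics in expectation. It says nothing about differences that arise in recruitment after it.

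**3. Can the screen miss a risk factor?** The article says the screen is to find variables that differ between groups, so take it as a comparison of arms. Assumed example: a factor present in 4% versus 3% of 1,422 per arm.

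- SE = √(2×0.035×0.965/1,422) = 0.00689; z = 0.01/0.00689 = 1.45; p ≈ 0.15. It is left out.

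One such factor biases little. If it multiplies risk 3-fold or 5-fold (assumed), the risk ratio it induces is (1+2×0.03)/(1+2×0.04) = 0.98 or (1+4×0.03)/(1+4×0.04) = 0.97. Three independent factors of this kind, all in one direction, give 0.98148³ ≈ 0.95 or 0.96552³ ≈ 0.90.

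**4. What would a residual difference do?** Assume no true effect, control 3.5%, no adjustment, and a pooled z test with effective n = 1,307 per arm. P(reject) = Φ[(d − 1.96·SE₀)/SE₁] + Φ[(−d − 1.96·SE₀)/SE₁], where d is the risk difference, SE₀ the pooled and SE₁ the unpooled standard error.

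| Underlying risk, experimental arm | d | SE₀ ≈ SE₁ | Two-sided rejection |
|---|---|---|---|
| 3.50% (equal) | 0 | – | 5.0% |
| 3.15% (10% lower) | 0.0035 | 0.00701 | 0.0720 + 0.0070 = 7.9% |
| 2.80% (20% lower) | 0.0070 | 0.00683 | 0.1747 + 0.0014 = 17.6% |

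**5. Room for covariates.** Expected events under the planning assumptions: 1,422×0.035 + 1,422×0.0175 = 49.8 + 24.9 ≈ 75.

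**The case against.** **The plan already looks for imbalance.** It has a baseline table, covariates in the primary model and a propensity score analysis. This stands as mitigation. A large imbalance in one measured variable would be found: 50% versus 35% gives SE = √(2×0.425×0.575/1,422) = 0.0185 and z = 0.15/0.0185 = 8.1. The rejection rates above therefore describe only what is left after adjustment, not the planned analysis as a whole. What does not go away is that the screen depends on the data, and that the propensity score does not enter the primary result.

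**The screen might be meant against the outcome.** The wording allows this, since it is the primary outcome that is put through the univariate regression. Strong factors would then usually pass: the factor in step 3, at a prevalence of 3.5% and a 3-fold risk ratio, would have 9.8% versus 3.3% events, z ≈ 3.5. The 4% versus 3% example applies to the other reading. On either reading the adjustment set is unknown until the outcome data are in hand.

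**Stronger readings that the documents do not support.** A reader might infer that staff see the scores before deciding whom to enrol, or that centres pick their patients. The text points the other way: scoring applies to patients already called eligible, both arm definitions refer to all eligible patients, and consent must come before entry. A reader might also count the absence of screening logs or masked recruiters as a fault. A journal article commonly leaves these to the full protocol, so their absence here is no finding. Nor is the life-expectancy criterion an error: it applies to both arms, and shows only that eligibility involves judgement.

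**Conclusion.** The point holds as one about a stated assumption and the covariate rule that goes with it. In a trial that recruits patients after cluster allocation, baseline thrombotic and bleeding risk is a potential confounder that can be named in advance, and the sentence to the contrary should not stand.

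The size is not known. Rejection of about 8% or 18% rests on an assumed residual risk difference of 10% or 20%, with no true effect and no adjustment. A reader might take these figures as the trial's false-positive rate; they are not. The bias could as well run against the scores as for them, and differences of this order would not by themselves produce the planned 50% reduction. That staff know the arm is inferred from the open procedure. Nothing in the article shows that selective enrolment has occurred.

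**What to change.** In Statistical Analysis:

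1. Delete the sentence on a priori confounders. State instead that patients are recruited after cluster allocation, so that baseline risk may differ between arms.
2. Replace the p ≤ 0.10 screen with a short covariate set, fixed before the data are analysed and included in the primary multilevel model whatever the p-values. Draw it from items collected in both arms, for example age, previous VTE, recent bleeding, mobility, major comorbidity, renal function and platelet count. The recorded Padua and IMPROVE scores cannot serve, as they exist in one arm only.
3. Report baseline risk by arm beside the primary result, and acknowledge that unmeasured selection would remain.

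The cost is wording and a few model degrees of freedom. With about 75 expected events the list has to stay short. No patients, visits or data items are added.

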#### Definition of the Experimental Group

This group includes those centers randomized to systematically evaluate VTE prophylaxis in all eligible patients using the Padua Prediction Score and IMPROVE Bleeding Score within 48 hours from hospitalization.

#### Definition of the Control Group

This group includes those centers randomized to evaluate VTE prophylaxis in all eligible patients based on clinical judgement only.

#### Definition of Dropout Criteria

Patients starting a de novo anticoagulant treatment during the time of hospitalization are excluded.

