The latter, however, has a limited support from the available literature. In addition, it should be underlined that in-hospital VTE and/or hospital readmission for VTE represent an important medical cost for the health care system.
32
33

Given the scarcity of randomized trials assessing the benefit of RAM- versus clinical judgement-guided VTE prophylaxis, the RICO study aims to evaluate which approach might reduce the composite, long-term incidence of these complications in hospitalized, acutely ill medical patients during hospital stay and after discharge. The results of this trial are expected to increase the knowledge on this topic. In particular, whether a RAM-guided strategy will result in improved outcomes, the study will contribute to strengthen the systematic use of Padua Prediction Score and IMPROVE Bleeding Score in the routine clinical practice.

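### The dropout rule for patients who start anticoagulant treatment in hospital contradicts the intention-to-treat analysis and, read literally, removes treated in-hospital VTE, which is a primary-outcome event

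*Protocol article*

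**What the plan says.** The dropout rule is one sentence: "Patients starting a de novo anticoagulant treatment during the time of hospitalization are excluded" (Definition of Dropout Criteria). It depends on what happens during the stay, so it applies after enrolment. It is separate from the eligibility criterion that keeps out patients if "they had any indication for anticoagulant therapy" (Exclusion Criteria).

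Two other sections keep everyone. Statistical Analysis: "All primary analyses will be on an intention-to-treat basis including all randomized participants". Study Procedures: "All patients, irrespective of allocation arm, are assessed at a 90-day follow-up". Since centres are the randomized units, the natural reading of the first is all patients enrolled at randomized centres.

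On the outcome, the Abstract (Methods) says: "The primary study outcome is a composite of symptomatic objectively confirmed VTE and major bleeding at 90-day follow-up". The Discussion describes the target as "the composite, long-term incidence of these complications in hospitalized, acutely ill medical patients during hospital stay and after discharge". Observation and Measurements collects confirmed VTE during the stay for each enrolled patient. Study Endpoints lists as a secondary endpoint "the evaluation of clinical outcomes (VTE, major bleeding, cardiovascular events) at the time of hospital discharge".

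**The concern.** A symptomatic in-hospital VTE is itself a reason to start anticoagulant treatment. A patient in that position meets both the primary outcome and the dropout criterion, and nothing in the article says which prevails. If the dropout rule prevails, patients leave the trial because they had the event that the trial counts. The secondary endpoint of VTE at discharge loses the same cases.

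Two things are at stake. The first is power: the outcome is rare, and in-hospital VTE is the part that in-hospital prophylaxis most directly influences. The second is bias. If the risk-score strategy prevents in-hospital VTE, control centres lose more events than experimental centres, and the estimate moves toward no difference. Treating staff also know whether their centre applies the scores when they decide on anticoagulation, so the exclusion is not protected from knowledge of the arm.

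**Working it through.** **Inputs from the Sample size section.** Control risk 3.5%; 50% reduction, so 1.75% in the experimental arm; two-sided 5%; 80% power; intracluster correlation 0.001; 16 clusters of at least 90 per arm; 2,844 patients in total.

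**1. The plan's own figures.**
- Two-proportion formula, pooled variance: 1,310 per arm (unpooled: 1,306.3).
- Design effect: 1 + (90 − 1) × 0.001 = 1.089.
- Per arm: 1,310 × 1.089 = 1,427, or 15.9 clusters of 90, rounded up to 16. The cluster count reproduces.
- Power at 16 × 90 = 1,440 per arm: 80.4%.
- Power at 2,844 in total (1,422 per arm, mean cluster size 88.9, design effect 1.088): 79.9%. This is the baseline for steps 2 and 3.
- Unpooled total before dropout: 2 × 1,306.3 × 1.089 = 2,845. So 2,844 matches the size before the 5% dropout allowance. The present point does not depend on this.

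**2. Equal proportional loss in both arms.** Let f be the share of primary events that are in-hospital VTE treated with an anticoagulant. The documents do not give f, so it is an assumption. These patients leave numerator and denominator:

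risk after exclusion = p(1 − f) / (1 − pf)

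For f = 25%, control: 0.035 × 0.75 / (1 − 0.00875) = 2.65%. Experimental: 0.0175 × 0.75 / (1 − 0.004375) = 1.32%.

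| f | control | experimental | power |
|---|---|---|---|
| 0 | 3.50% | 1.75% | 79.9% |
| 10% | 3.16% | 1.58% | 75.9% |
| 25% | 2.65% | 1.32% | 68.4% |
| 50% | 1.78% | 0.88% | 51.7% |

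The risk ratio stays near 0.50, so the cost here is power alone. A 5% dropout allowance does not cover it. At f = 50% only 0.035 × 0.5 = 1.75% of control patients are removed, but they carry half of the control events.

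**3. Unequal loss.** Assume that in-hospital VTE falls by 75% in the experimental arm and that the overall reduction is still 50%. For f = 30%:
- Control: in-hospital VTE 0.30 × 3.5% = 1.05%; other events 2.45%.
- Experimental: in-hospital VTE 0.25 × 1.05% = 0.2625%; other events 1.75% − 0.2625% = 1.4875%.
- After exclusion: control 0.0245 / (1 − 0.0105) = 2.48%; experimental 0.014875 / (1 − 0.002625) = 1.49%.
- Observed risk ratio 0.60; power 44%.

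The same steps at f = 50% give 1.78% against 1.32%, risk ratio 0.74, power 16%.

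**The case against.** The strongest reply is that the article as a whole seems to want these events counted. It collects in-hospital VTE for each enrolled patient, sends the records to an Adjudication Committee, assesses all patients at 90 days and analyses by intention to treat. On that view the dropout sentence only extends the baseline exclusion to new indications other than VTE, and a VTE exception may stand in the full protocol. This supports caution about what was done in practice, but it does not remove the contradiction. The article nowhere limits the rule to non-VTE indications, and an unqualified exclusion cannot be true together with an analysis that includes everyone.

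Two limits on wording stand. The rule says anticoagulant treatment, which most naturally means therapeutic use and not the prophylaxis under study, although the term is not defined. And the analysis section describes the outcome as "proportion of thromboembolic and hemorrhagic events at a 90-d follow-up after hospital discharge", which blurs the start of the window; the Discussion and the data-collection section support counting events during the stay.

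A reader might go further and infer that primary events will certainly be deleted, or that the rule would erase the effect altogether, with a risk ratio near 1. The documents support neither. Deletion follows from a literal reading and is not stated. A risk ratio near 1 requires the whole benefit to lie in in-hospital VTE. Since the planned reduction is 1.75 points out of 3.5, in-hospital VTE would have to make up at least half of all primary events and be almost entirely prevented. A reader might also take this for a rule about centres because centres are randomized, but its subject is patients.

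**Conclusion.** The point holds as a contradiction on the face of the article. A post-enrolment exclusion with no VTE exception conflicts with the stated analysis population and the stated follow-up. Applied as written, it removes patients who have had a primary event. Either meaning of exclusion does harm: from analysis, it breaks intention to treat; from follow-up, it loses the promised 90-day outcomes.

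The size is conditional. The power figures rest on assumed values of f and on every such patient being dropped. The shift in the risk ratio rests further on the assumed 75% reduction in in-hospital VTE. The direction toward no difference needs only that the strategy prevent a larger proportion of in-hospital VTE than of other primary events. The matter should be settled before analysis because the exclusion is tied to the outcome itself.

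**What to change.** Reconcile Definition of Dropout Criteria, Study Procedures and Statistical Analysis so that they say the same thing:
- every enrolled patient stays in the primary analysis under the centre's arm;
- a VTE or major bleeding event is counted, whether or not anticoagulant treatment was started;
- follow-up runs to day 90 for patients who start such treatment;
- patients who started anticoagulant treatment for a reason other than VTE are set aside only in a sensitivity analysis.

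This concerns the analysis population and data collection only and changes no treatment. The cost is a wording amendment, plus retaining or retrieving in-hospital and 90-day data for any patients already dropped. No new patients are needed for this change. Some of the 90-day data may not be recoverable; the number affected should then be reported by arm.
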